**Methods:**

A randomized controlled trial (RCT) design with repeated measures will be used to evaluate the effectiveness of MBCT to treat psychological distress in pregnancy. A sample of 60 consenting pregnant women aged 18 years and above will be enrolled and randomized to the experimental (MBCT) or control (treatment as usual) condition. Primary (e.g., symptoms of stress, depression, and anxiety), secondary (cortisol, blood pressure (BP), heart rate variability (HRV), and sleep) and other outcome data (e.g., psychological diagnoses) will be collected via a combination of laboratory visits and at-home assessments from both groups at baseline (T_1_), immediately following the intervention (T_2_), and at 3 months postpartum (T_3_). Descriptive statistics will be used to describe sample characteristics. Data will be analyzed using an intention-to-treat approach. Hierarchical linear models will be used to test intervention effects on primary and secondary outcomes.

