### Three hypotheses

Primary hypotheses for the trial are:When compared to a TAU control group, women who receive MBCT during pregnancy will, on average, experience lower symptoms of depression, worry, anxiety, and perceived stress over the course of the study

Secondary hypotheses for the trial are:2.When compared to a TAU control group, women who receive MBCT will, on average, have lower levels of cortisol, lower BP, exhibit lower BP stress reactivity, have lower HRV and will have better sleep over the course of the study

Exploratory hypotheses for the trial are:3.Initial levels of psychological distress will moderate findings, such that a larger treatment effect will be observed among women with higher psychological distress at baseline

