### Sample size

Based on the findings from a previous study, which examined the impact of a MBI during pregnancy on prenatal stress and mood, we expected a medium effect size of Cohen’s *d* = 0.5 [44] for the outcomes of PRA, anxiety, and depression for pre-post testing. Using a two-tailed test and a .05 significance level, 21 participants in each group (42 total) would provide adequate power (95 %) to reject the null hypothesis [103]. With an estimated attrition rate of 20 %, the number of participants required becomes a minimum of 26 participants per group (total *N* = 52).

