### Statistical analyses

Baseline characteristics (demographic and psychological) will be compared between groups using *t* tests (means) for continuous variables and chi-squared tests (%) for categorical variables to ensure randomization success. Any covariates found to differ significantly between groups will be held constant in between-group analyses. A significance level of .05 will be used for tests of all research hypotheses. The outcomes are between-group differences from baseline (T_1_) to post-intervention points (T_2,3_) on psychological and physiological measures. Analyses will be completed using Hierarchical Linear Modeling (HLM). HLM is a flexible approach to analysis of repeated measures data. For example, unlike analysis of variance (ANOVA), linear mixed models do not require that each participant has complete data to be included in the analysis, thus increasing their statistical power [104, 105]. All analyses will be completed using an intention-to-treat (ITT) approach—all participants will be included in the final statistical analysis according to the group (MBCT or TAU) to which they were randomized. To assess the effects of baseline psychological distress on outcomes, separate hierarchical mixed models of each outcome will be conducted using pretreatment psychological distress as a potential moderator.

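### Baseline symptom scores are adjusted for only if they differ significantly between arms; every outcome model should account for its own baseline value, and one primary contrast should be fixed

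*Protocol article*

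**What the plan says.** All references are to the protocol article.

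- **Statistical analyses, outcome definition:** "The outcomes are between-group differences from baseline" (T1) to T2 and T3, for both the psychological and the physiological measures. Neither T2 nor T3 is named as primary, and no averaged effect is defined.
- **Statistical analyses, baseline rule:** demographic and psychological characteristics at baseline are compared between arms by t test or chi-squared test. Those with a significant difference are then held constant in the between-group analyses. This is the only rule given for baseline adjustment.
- **Statistical analyses, model:** hierarchical linear modelling, by intention to treat. How the baseline value of the outcome enters the model is not stated.
- **Three hypotheses:** women given MBCT will "on average, experience lower symptoms of depression, worry, anxiety, and perceived stress over the course of the study".
- **Sample size:** "we expected a medium effect size of Cohen’s *d* = 0.5", stated "for the outcomes of PRA, anxiety, and depression for pre-post testing". From this the section derives 21 women per group for 95 % power, then 26 per group after 20 % attrition. The Abstract gives an enrolment of 60.

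**The concern.** Under proper randomisation, a significant baseline difference is a chance event. Testing for one says nothing about which covariates are worth adjusting for; that depends on how strongly they predict the outcome. The baseline value of a symptom scale is usually the strongest predictor available, and this trial collects it from every woman before randomisation. Under the stated rule it is used for adjustment only when the test comes out significant.

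Two things follow. The model is not fixed in advance: the four primary scales could end up with different models because of chance imbalance, and the reported standard errors take no account of that selection step. In the usual case, with no significant imbalance, the comparison falls back on an unadjusted difference in change, which is less precise than it need be. In a trial of 60 women this matters.

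A related looseness is that the hypothesis, the power basis and the outcome definition describe the comparison in different words, and no visit is primary. A result that is positive at T2 and null at T3, or the reverse, could be read either way.

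**Working it through.** **1. The plan's own figure.** Inputs from Sample size: d = 0.5, two-sided 0.05, 21 per group. As a two-group comparison with unit SD, power = Φ(0.5/√(2/21) − 1.96) = Φ(1.620 − 1.960) = 36.7 % (35.3 % with the t distribution). A power of 95 % needs 2 × (1.960 + 1.645)²/0.25, or 104 per group. The stated 95 % is therefore not reproduced. It is approached (94.6 % at 42 in total) by entering f = 0.25 for a group-by-time interaction with three visits and a correlation of 0.5. Those inputs are not stated, and they imply a difference in change of about 1.06 SD rather than 0.5.

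**2. How often the rule would adjust.** Assume the baseline tests also use 0.05. Under randomisation, each score is then adjusted for about 5 % of the time and left out about 95 % of the time. If the four primary scales were independent, at least one would be adjusted with probability 1 − 0.95⁴ = 18.5 %. Correlated scales would change that figure.

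**3. Variance with and without the baseline value.** Assumptions: SD of 1 at each visit, equal correlation ρ between visits, complete data. The article gives no ρ, so the range 0.3 to 0.8 is shown. The variance of the arm difference is 2v/n, with n per arm and v as follows.

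- One visit: unadjusted change v = 2(1 − ρ); baseline accounted for v = 1 − ρ². Ratio (1 + ρ)/2.
- Mean of T2 and T3: unadjusted change v = (1 + ρ)/2 + 1 − 2ρ = 1.5(1 − ρ); baseline accounted for v = (1 + ρ)/2 − ρ². Ratio (1 + 2ρ)/3.

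| ρ | One visit, ratio | Reduction | Mean of T2/T3, ratio | Reduction |
|---|---|---|---|---|
| 0.3 | 0.65 | 35 % | 0.53 | 47 % |
| 0.5 | 0.75 | 25 % | 0.67 | 33 % |
| 0.7 | 0.85 | 15 % | 0.80 | 20 % |
| 0.8 | 0.90 | 10 % | 0.87 | 13 % |

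Both ratios are below 1 for any ρ below 1. A generalised least squares calculation for three visits, with baseline means free or constrained equal, gives the same ratios.

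**4. What this means for power.** Power = Φ(0.5/√(2v/21) − 1.96), for a true difference of 0.5 SD. The mean-of-T2/T3 columns assume that this difference holds at both visits.

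| ρ | One visit, change | One visit, baseline accounted for | Mean T2/T3, change | Mean T2/T3, baseline accounted for |
|---|---|---|---|---|
| 0.3 | 27.7 % | 39.7 % | 35.2 % | 58.1 % |
| 0.5 | 36.7 % | 46.4 % | 46.4 % | 63.0 % |
| 0.7 | 55.2 % | 62.1 % | 67.6 % | 77.0 % |
| 0.8 | 72.6 % | 77.0 % | 84.1 % | 88.8 % |

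Enrolling 60 with 20 % attrition leaves 60 × 0.8 / 2 = 24 per arm. At ρ = 0.5 the four columns then become 41 %, 52 %, 52 % and 69 %. At ρ = 0.5, 95 % power needs 104 (change) or 78 (baseline accounted for) per group at one visit, and 78 or 52 for the mean of T2 and T3.

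**The case against.** The strongest reply is that the article never says baseline is handled badly. It names a hierarchical model and differences from baseline, and a model with constrained baseline means also estimates such differences. Parameterisation is normally left to a fuller plan. That stands in part: the unadjusted change contrast used as comparator above is an assumption about what would be run. The significance-test rule, however, is stated, and it is the only baseline adjustment stated. A fuller plan would have to override it rather than fill a gap.

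A second reply is that the size of the gain rests on a correlation nobody has stated. That is correct, and it is why a range is given. The direction does not depend on it.

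A third is that making T2 the sole primary contrast brings no sure gain in power. That also stands. T2 with baseline accounted for ties with the unadjusted mean change over T2 and T3 at ρ = 0.5 (46.4 % each). It is weaker above that (62.1 % against 67.6 % at 0.7) and stronger below (39.7 % against 35.2 % at 0.3). T3 was also timed to postpartum onset of mood disorder, so the choice between contrasts is one of purpose.

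A reader might go further and infer that the article plans three conflicting contrasts, among them a group main effect averaged over T1 to T3, or that it plans a linear time slope across unevenly spaced visits. The text does not support this. In Hypothesis 1, on average can simply mean the group mean. Pre-post is most naturally one component of the T2 and T3 outcomes. No section plans a T1 to T3 main effect or a linear slope.

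**Conclusion.** The point holds in a limited form. The stated baseline rule makes adjustment for the outcome's own baseline value depend on a significance test. That leaves the model unfixed and gives up precision that is free to recover: 35 % to 10 % of the variance at one visit and 47 % to 13 % for the mean of T2 and T3, for correlations from 0.3 to 0.8. These figures assume equal SDs, equal correlations and complete data, and take an unadjusted change contrast as comparator. The issue is precision and prespecification: under randomisation the unadjusted contrast is itself unbiased.

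The hypothesis, power basis and outcome definition are loosely aligned rather than contradictory, and no primary contrast is fixed. That calls for clarification.

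It would be wrong to infer that better baseline handling restores the planned power. At 21 per group, power with baseline accounted for runs from 39.7 % to 88.8 % over the cases shown, and never reaches 95 %. The Sample size figure is a separate problem.

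**What to change.** 1. Replace the baseline significance-test rule. For every outcome, fit the mixed model with visit as a categorical factor and the baseline value of that outcome always accounted for, either by constraining baseline means to be equal across arms or by entering baseline as a covariate. Choose one form in advance and use it throughout. Baseline characteristics can still be tabulated, without tests.
2. Name one primary contrast, MBCT minus TAU, either at T2 or for the mean of T2 and T3. The sponsor should choose according to whether the main question is benefit after the course or benefit carried into the postpartum period.
3. Word Hypothesis 1, Sample size and Statistical analyses to match that contrast, and state the correlation assumed when the sample size is recalculated for it.

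The cost is a change of wording in the protocol or analysis plan, made before outcomes are examined by arm. No extra data, visits or software are needed.

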### Day-to-day trial management

[name] (PI) will be responsible for overall project management. A full-time research coordinator has been hired and is responsible for the day-to-day trial management under the supervision of [name]. We have received ethics approval for the study and all materials, including questionnaires and consent forms, have been prepared. The MBCT protocol, as well as all handouts, audio-recordings, and videos were developed by [name] team and have been modified to include information about stress and anxiety management. Currently, staff are hired and trained. Graduate students have been trained in the administration of the SCID and we have established an ongoing reliability team supervised by a licensed clinical psychologist. All data will be stored in a locked, secure area at the University of Calgary. Any paper work with patient identifiable data (e.g., consent forms, case notes, contact information) will be stored separately from anonymized data. Patient confidentiality will be protected through all phases of assessment, treatment, and data analysis in line with University of Calgary ethics guidelines. We expect to be have completed follow-up visits by April 2017.

### Access to data and dissemination policy

As the primary investigator on the trial, [name], will remain the custodian of the data collected during the trial. Data will not be released by any third party (including the funder) before trial completion and will be analyzed independently by the study team. No interim analyses are planned and no interim data will be shared. Recognizing the importance of sharing results, data will be shared in accordance with the International Committee of Medical Journal Editors’ guidelines, which state that authors share with others the deidentified individual patient data underlying results presented in the trial reports (including tables, figures, and appendices or supplementary material) no later than 6 months after publication. Data will be made available upon request to the first author.

## Discussion

Perinatal mood disorders are highly prevalent, and their burden is significant. Clinically significant psychological distress in pregnancy is one of the best predictors of postpartum mood disorders, which are associated with numerous negative outcomes for the mother, the child, and the attachment relationship [24]. Depression and anxiety in pregnancy have also been associated with poor obstetrical outcomes and appear to predict infant health problems [22, 106] and mental health problems in children and adolescents, even after controlling for maternal postpartum mood. MBCT is a promising method for reducing symptoms of psychological distress and preventing the development of postpartum mood disorders [49–53]. Despite this, there are few rigorous examinations of MBCT in the perinatal period, and none to date that examine potential changes in maternal physiology.

Limitations of this study include the use of a TAU control group, whereby women enrolled on the trial are free to pursue services for the treatment of psychological distress experienced in pregnancy. It is also possible that women randomized to either group may seek out pharmacological and/or psychological interventions for the treatment of psychological distress and this may limit our ability to detect group differences between MBCT and the control condition. However, the decision to use a TAU control group was made due to ethical considerations, as we did not wish to discourage pregnant women from seeking treatment while experiencing active distress. In order to control for other treatment potentially sought by participants, we are collecting data about alternative types of treatment that women pursued while in the study. An additional limitation is that the group recruited will be a heterogeneous sample that will have varying levels of psychological distress and diagnostic profiles. While this methodological decision was made to enhance external validity, it may reduce internal validity. In spite of its limitations, this project is one of few aimed at assessing both the potential psychological and physiological changes associated with evidence-based mindfulness interventions delivered in pregnancy. The current study design also has a number of strengths, including: (1) interviewer-assessed clinical diagnosis of psychological disorders, (2) longitudinal study design with follow-up that extends into the postpartum period, and (3) extensive physiological testing, including assessment of BP, HRV, stress reactivity, HPA function, and sleep.

## Trial status

This study is recruiting participants.

## Abbreviations

ANOVA: Analysis of variance
BP: Blood pressure
CBT: Cognitive behavior therapy
DSM: Diagnostic and Statistical Manual of Mental Disorders
ECG: Electrocardiography
EDS: Edinburgh Depression Scale
GAD: Generalized Anxiety Disorder
HLM: Hierarchical Linear Modeling
HPA: Hypothalamic-pituitary axis
HRV: Heart rate variability
IPT: Interpersonal therapy
ITT: Intention-to-treat
MBCT: Mindfulness-based Cognitive Therapy
MBCT-PD: Mindfulness-based Cognitive Therapy adapted for perinatal depression
MBSR: Mindfulness-based Stress Reduction
MBI: Mindfulness-based Intervention
PRA: Pregnancy-related anxiety
RCT: Randomized controlled trial
TAU: Treatment as usual
